#### Additional information

If available, blood inflammatory markers (e.g. leukocyte counts) will be retrieved from the medical records of participating patients. Furthermore, clinical information derived from the questionnaire will be completed with relevant data from the medical records.

#### Data management

All clinical data collected will be collected in an electronic case report form (eCRF) using the clinical data management platform CASTOR. Personal data will be handled with strict care and following Good Clinical Practice (GCP) guidelines. Collected data and samples will be coded with a pseudonymized study code, the key linking study code to patient data will only be accessible to the primary investigator as well as the coordinating researcher(s). Conform current guidelines, all data and samples will be stored for a maximum of 15 years and can be used for any future studies in line with the current research.

### Statistical and bioinformatic analyses

#### Sample size calculation

The sample size calculation was based on having sufficient precision to estimate sensitivity and specificity of the GUS activity assay to predict late-onset GI toxicity. Literature shows that about 82% of patients treated with irinotecan experience diarrhea (all grades) [25], while approximately 18% develop grade 3–4 diarrhea [5, 6]. For estimation of sensitivity, we determined a maximum half-width of the 95% confidence interval (CI) of 17%, requiring a minimum of 22 patients with grade 3–4 diarrhea. To achieve this precision, a total of 84 patients need to be included, considering an estimated toxicity rate ranging from 16 to 22%. Out of these 84 patients, 62 individuals would not experience grade 3–4 diarrhea, allowing for the estimation of specificity with a 95% CI half-width of around 10%. Hence, the total number of patients required remains at 84. Considering an anticipated 20% drop-out rate, because of the advanced setting, 104 patients need to be included in the study.

#### Statistical and bioinformatic analysis of main outcome parameters

The association between CMS subtypes 1–4 and treatment response (categorized as progressive disease, stable disease, partial response and complete response) will be analyzed using chi-squared tests. Survival analysis within the different CMS subtypes will be done by Kaplan Meier curves.

To validate the safety of the 70% irinotecan starting dose intensity, toxicity in UGT1A1 PMs will be compared to historical control patients, i.e. cohorts of patients described in literature that are homozygous polymorphic for *UGT1A1*28* and were treated with full dose therapy. In addition, toxicity in UGT1A1 PMs will be compared to UGT1A1 non-PMs treated with full dose in the current study, under the assumption that these groups experience comparable degrees of toxicity.

Correlations between GUS activity and the degree of experienced late-onset GI toxicity during irinotecan-based treatment will be analyzed by means of the Spearman correlation coefficient. Furthermore, we will investigate whether GUS activity is different between patients without diarrhea vs. grade 1–2 diarrhea vs. grade 3–4 diarrhea by means of ANOVA or the Kruskal Wallis test, depending on whether the data are normally distributed or not. Longitudinal changes in GUS activity during irinotecan-based treatment will be analyzed using repeated-measures ANOVA or the Friedman test.

Bioinformatic analysis of the predicted GUS functionality derived from metagenomics sequencing will be conducted. A Hidden Markov Model (HMM)-profile will be made per orthologous group with predicted GUS functionality, based on a reference dataset of publicly available GUS protein sequences and the results of Pollet et al. [12, 26]. The HMM-profiles will be used to identify all predicted proteins with a potential GUS functionality per fecal sample. These predicted proteins will be used to create a non-redundant microbial GUS protein catalogue.

Changes in GUS activity and overall gut microbiota composition, diversity and potential GUS capacity during irinotecan-based systemic treatment will be assessed by redundancy analysis (RDA) [27] and ANOVA [28]. These data will be used to examine the microbial GUS variation and origin per fecal community in order to link the microbial composition and GUS functional potential to the measured GUS activity.

In addition, the main outcome parameters will be correlated to fecal levels of SN-38 and SN-38G, as well as other clinical variables of interest, as assessed by the questionnaires.

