## Background

Colorectal cancer (CRC) represents a major public health concern as it is the third most frequently diagnosed cancer and the second cause of cancer-related mortality worldwide [1]. In 2022, 21% of patients with newly diagnosed CRC in the Netherlands suffered from metastatic disease [2]. In this group of patients, irinotecan-based systemic treatments are commonly applied to relieve symptoms, improve quality of life (QoL) and extend overall survival (OS).

However, the individual response to irinotecan-based treatment differs consistently between patients, and is currently largely unpredictable. Previous research indicated that molecular tumor characteristics might be associated with response to irinotecan-based systemic treatment. CRC can be subdivided into four consensus molecular subtypes (CMS1-4), based on different gene expression profiles [3]. Ten Hoorn et al. concluded based on a meta-analysis that specifically in CMS4 metastatic disease, patients benefit more from irinotecan-based regimens compared with oxaliplatin-containing regimens [4].

An additional disadvantage of irinotecan-based systemic treatment is the occurrence of systemic (primarily neutropenia) and late-onset gastrointestinal (GI) toxicity, (primarily diarrhea). For instance, grade 3–4 neutropenia has been previously identified in 46% and grade 3–4 diarrhea in approximately 18% of patients [5, 6]. The occurrence of severe toxicity often leads to irinotecan dose reduction, or premature discontinuation of the treatment. This negatively affects not only the patient’s QoL and OS, but also puts significant pressure on family and caregivers, as well as on hospitalization-related healthcare costs [7]. Consequently, there is an urgent need for biomarkers to identify patients at risk for developing irinotecan-induced toxicity. In this context, two promising candidate biomarkers are 1) the UDP Glucuronosyltransferase Family 1 Member A1 (*UGT1A1*) genotype of the patient and 2) the microbial enzyme β-glucuronidase (GUS).

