## Methods and study design

### Aims of the study

The primary objectives of this study are:To investigate whether tumor molecular markers can predict the response to irinotecan-based systemic treatment and are associated with QoL and OS;To validate the safety of *UGT1A1* genotype-guided dose adaptation (70% dose intensity) in UGT1A1 PMs;To assess whether high bacterial GUS enzyme activity is associated with irinotecan-induced GI toxicity, decreased QoL and OS

The most important secondary objectives of this study are:To investigate the dynamics in GUS activity and overall gut microbiota composition, diversity and functional capacity during irinotecan-based systemic treatment;To assess associations between GUS activity and gut microbiota composition, diversity and functional capacity,To measure fecal levels of SN-38 and SN-38-G and to determine its association with gut microbiota composition, bacterial GUS activity, *UGT1A1* genotype, treatment response and toxicity;To correlate tumor molecular profile, GUS activity and other clinical characteristics (e.g. physical performance and nutritional status) during irinotecan-based systemic treatment.

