### Sample collection and analysis

#### Tumor molecular profiling

If archived tumor samples are available from prior surgery or biopsy, the molecular profile of the tumor will be quantified using RNA sequencing for CMS classification and a DNA panel for mutational characterization. Therefore, a workflow will be generated using DNA/RNA from formalin-fixed paraffin-embedded (FFPE) tissues. These samples will be analyzed using RNA sequencing and the TruSight Oncology 500 (TSO500) assay, utilizing the Illumina NovaSeq6000 platform. The CMS classification of the tumor will be characterized based on a recently established FFPE CMS classification algorithm [19]. The TSO500 targets somatic variants over 523 relevant cancer genes.

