### Clinical data collection and management

#### Evaluation of tumor response

Tumor response will be evaluated based on standard care CT or MRI scans conducted at baseline (T1) and after the fourth cycle (T5) of irinotecan-based systemic therapy. Based on the percentage of change of target lesions, tumor response will be scored according to the Response Evaluation Criteria in Solid Tumors (RECIST, version 1.1 [23]) and will be classified as progressive disease, stable disease, partial response or complete response.

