## Discussion

To the best of our knowledge, the OPTIMA study will be the first study to evaluate tumor molecular profiling, *UGT1A1* genotype and GUS activity as potential biomarkers for efficacy and toxicity of irinotecan-based systemic treatment in patients with advanced CRC. By combining these three biomarkers into one study, we will provide pivotal new insights for clinicians to make well-considered choices concerning for instance the initiation, dose adjustments or the need for microbiota modulation during irinotecan-based systemic treatment in this patient population.

The tumor molecular profiling will provide new insights into which patients are expected to benefit from irinotecan-based systemic treatment. As outlined in the introduction, irinotecan-based systemic treatment is probably not the optimal choice in all CMS subtypes. Validation of these previous findings in the current cohort will significantly strengthen the rationale for a more personalized treatment selection based on the tumor molecular profile.

Furthermore, OPTIMA will further evaluate the use of *UGT1A1* genotype and subsequent dose adjustments in clinical practice. If a 70% dose intensity in UGT1A1 PMs leads to similar incidences of severe toxicity as compared to UGT1A1 NMs and IMs treated with the full dose, this further supports the validity and utility of this biomarker.

In addition, new knowledge on the role of bacterial GUS in a clinical setting, will enhance the detection of patients who are expected to experience high GI toxicity before start of the treatment. This opens the opportunity to modulate GUS activity in these patients by targeted gut microbiota modulation.

However, there are some limitations inherent to the current study. Due to the inclusion of patients receiving different treatment regimens, as well as potential treatment delays in individual patients, the time between two consecutive sampling time points might differ between patients. Additionally, we only ask patients to report overall dietary patterns and do not collect detailed data on dietary intake, which might influence particularly the gut microbiota parameters. Lastly, due to the advanced setting, patients might have distinct and complex medical histories, co-morbidities and co-medication which could influence the outcomes.

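### The planned chi-squared test of CMS1–4 against RECIST category ignores the order of response on a sparse 4×4 table; an ordinal test across the four subtypes would usually have more power

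*Protocol article*

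**What the plan says.** The first-listed primary objective (Aims of the study) is "To investigate whether tumor molecular markers can predict the response to irinotecan-based systemic treatment". Under Evaluation of tumor response, each patient "will be classified as progressive disease, stable disease, partial response or complete response". The section on statistical analysis of main outcome parameters names the test for the four CMS subtypes: "treatment response (categorized as progressive disease, stable disease, partial response and complete response) will be analyzed using chi-squared tests". It names no ordinal method, no collapsing of categories, no exact version and no contrast between particular subtypes.

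Three other places bear on this:
- **Number of patients.** The sample size section sizes the study for the precision of the GUS assay and concludes "Hence, the total number of patients required remains at 84", raised to 104 enrolled for 20% drop-out. It gives no power or effect size for the CMS analysis.
- **Tissue.** Profiling is conditional: "If archived tumor samples are available from prior surgery or biopsy". No availability rate is given.
- **CMS4.** The Background cites a meta-analysis finding that "specifically in CMS4 metastatic disease, patients benefit more from irinotecan-based regimens compared with oxaliplatin-containing regimens". The Discussion adds: "Validation of these previous findings in the current cohort will significantly strengthen the rationale for a more personalized treatment selection".

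**The concern.** RECIST response runs from progressive disease through stable disease and partial response to complete response. A chi-squared test treats these as four unrelated labels. Crossed with four subtypes, it spreads any difference over (4−1)×(4−1) = 9 degrees of freedom. An ordinal test across the four subtypes uses 3, and an ordinal contrast of one subtype with the rest uses 1.

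The table is thin for 16 cells, and the study was not sized for this question. Two consequences follow for a primary objective. A non-significant result would say little, because power against a sizeable shift is low. A significant one would not show which subtype differs, or whether its response is better or worse.

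**Working it through.** **1. Number of patients.** The stated target is 84 evaluable. With 20% drop-out, 84/0.8 = 105, close to the stated 104. The documents give no figure for the CMS table itself, so N = 60 (tissue missing for some), 84 and 104 (all enrolled) are used as a range.

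**2. Average cell count, no assumptions about margins.** 84/16 = 5.25. Even all 104 would give 104/16 = 6.5. Any CMS table with fewer than 16×5 = 80 patients averages below 5.

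**3. Expected counts with unequal margins.** The formula is E = N × (share of subtype) × (share of response category). The shares are assumptions:
- CMS1/2/3/4: 5/45/15/35%, 14/37/13/36% or 10/40/10/40%.
- Progressive/stable/partial/complete: 20/40/37/3%, 15/40/40/5% or 10/35/50/5%.

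Example at N = 84 with the second set of each: CMS2 with stable disease 84×0.37×0.40 = 12.4; CMS2 with progression 84×0.37×0.15 = 4.7; CMS3 with complete response 84×0.13×0.05 = 0.55. Over all nine combinations, 9 to 12 of 16 cells are below 5 and 2 to 4 are below 1.

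**4. Type I error.** With no difference between subtypes, the 4×4 chi-squared test rejected in 4.3–6.5% of simulated tables across the three sample sizes (nominal 5%). Sparsity does not materially invalidate the test.

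**5. Power if only CMS4 differs.** The response odds in CMS4 are shifted by a common odds ratio (OR) at every cut-point. For instance, 45% responders elsewhere is odds 0.45/0.55 = 0.818; times 3 is 2.45, or 71% responders in CMS4. There were 2,000 simulated tables per scenario, with an assumed two-sided 5% level. The range is over three pairings of CMS mix and response distribution.

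| N | OR | 4×4 chi-squared | Kruskal-Wallis, 4 subtypes | Rank-sum, CMS4 vs rest |
|---|---|---|---|---|
| 84 | 2 | 13–15% | 22–23% | 34–35% |
| 84 | 3 | 29–31% | 50–53% | 69–70% |
| 84 | 4 | 47–49% | 71–74% | 85–88% |
| 60 | 3 | 20–22% | 36–37% | 52–56% |
| 104 | 3 | 40% | 61–62% | 78–80% |

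A separate simulation at OR 3 and N = 84 gave 30–32%, 51–54% and 68–71%.

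**6. Power under other patterns.** N = 84, CMS mix 14/37/13/36%, response 15/40/40/5% in the reference subtypes, 3,000 tables each.

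| Pattern | 4×4 chi-squared | Kruskal-Wallis | CMS4 vs rest |
|---|---|---|---|
| CMS2 and CMS4 both better, OR 3 | 32% | 46% | 17% |
| Only CMS1 worse, OR 1/4 | 30% | 44% | 10% |
| Graded over subtypes, CMS4 best | 45% | 65% | 56% |
| CMS4 with more progression and more partial response (30/10/55/5%) | 51% | 4% | 7% |

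The ordinal test across four subtypes beats the chi-squared test in every ordered pattern tried and loses clearly in the non-monotone one. The CMS4-only contrast is best when CMS4 alone differs, but falls below the chi-squared test when other subtypes drive the difference.

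**The case against.** The strongest reply has four parts.

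- **This is a condensed article.** The plural 'tests' does not commit the study to one 9-degree-of-freedom test, and handling of small cells or contrasts may sit in an analysis plan that is not shown. This stands for the details. It does not cover the choice of method: the article names chi-squared tests on four response categories for a primary objective, and no version of that test on those categories uses their order.

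- **Validity is intact.** This stands. The simulated type I error supports it, so small expected counts are no ground for calling the p-value wrong.

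- **The power loss depends on assumptions.** This also stands. A reader might infer that the planned test throws away more than half the achievable power. The documents do not support that as a general statement. Against the CMS4 contrast at N = 84, the loss is 55–58% at OR 3 but 44–46% at OR 4; at N = 104 and OR 4 it is 32–35%. Against an ordinal test across all four subtypes it is about 40% at OR 3 and N = 84 (for example 1 − 30.9/50.4 = 39%). Nor is 84 a firm ceiling for this table: it is the GUS target, and a patient who stops giving fecal samples may still have tissue and scans.

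- **There is no CMS4 hypothesis to miss.** A reader might infer from the Background and Discussion that the plan fails to test its own CMS4 claim. The cited result compares irinotecan-based with oxaliplatin-containing regimens within CMS4. Everyone in this cohort receives irinotecan, and patients on FOLFOXIRI receive oxaliplatin as well, so no comparison of response between subtypes here can test it. The stated objective is general. CMS4 versus the rest is a reasonable question, but a different one, and making it the sole main test could cost more power than it gains.

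**Conclusion.** The point holds as one of efficiency and interpretability. The planned method ignores the order of RECIST response and spreads a small cohort over a sparse 4×4 table. The documents alone establish the ordering, the average of 5.25 patients per cell at N = 84 and the conditional use of tissue. The power figures rest on assumed CMS mix, response rates, effect size, significance level and, for the central comparison, a shift confined to CMS4. In that setting, replacing the unordered test by an ordinal one across the same four subtypes raises power from about 30% to 50–54% at OR 3. Even then power stays modest, so a non-significant result would still need to be read with its confidence intervals. The change is worth making but is not critical.

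**What to change.** Change the analysis wording for CMS and response as follows:

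1. **Main analysis:** an ordinal comparison of RECIST category across all four CMS subtypes, by Kruskal-Wallis test or proportional-odds model, with a permutation p-value if cells are sparse.
2. **Secondary analysis:** a pre-specified ordinal contrast of CMS4 versus the rest, reported as an odds ratio with 95% CI. State that it compares subtypes within irinotecan-treated patients and does not test the cited between-regimen result. Align the Discussion sentence on validating previous findings with this.
3. **Supportive:** the full 4×4 table with its chi-squared or exact test.

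No new patients, samples or scans are needed. The price is that an ordinal test has little power if a subtype shows both more progression and more response (4% against 51% in the pattern simulated). Keeping the 4×4 test as supportive covers that case.

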#### Study population

Patients will be included via the oncologic outpatient clinics of the participating centers. Patients are eligible if they are ≥ 18 years of age, diagnosed with advanced CRC, and planned to start with irinotecan-based systemic treatment, if applicable in combination with anti-EGFR treatment. Additionally, patients must have a WHO performance status 0–2, minimal acceptable safety laboratory values at baseline, defined as: ANC of ≥ 1.5 × 109/L, platelet count of ≥ 100 × 109/L, serum bilirubin ≤ 1.5 × ULN, ALAT and ASAT ≤ 2.5 × ULN; in case of liver metastases ALAT and ASAT ≤ 5 × ULN, and renal function (eGFR) ≥ 50 ml/min or creatinine ≤ 1.5 × ULN.

Exclusion criteria are: microsatellite instability (MSI) or deficient MMR proteins, being pregnant or nursing, presence of an ileostomy, Asian ethnicity, other systemic treatment within < 1 month before inclusion, therapeutic antibiotic use within < 3 months before inclusion, abdominal radiotherapy within < 2 weeks before inclusion, being physically or mentally incapable or incompetent, more than 25% irinotecan dose reduction at the start of treatment (dose reductions during treatment are allowed), with exception of dose reduction in UGT1A1 PMs.

Patients can be treated with combination chemotherapy (FOLFOXIRI/FOLFIRI) or irinotecan monotherapy and will follow the regular treatment regimens, according to the Dutch guidelines (Table 1).

**Table 1 Tab1:** Overview of irinotecan-based treatment regimens

		**Compounds**	**Number of weeks per cycle**	**Possible addition of bevacizumab?**	**Possible addition of anti-EGFR?**
Treatment	FOLFOXIRI	Irinotecan 5-FU Folinic acid Oxaliplatin	2	yes	no
	FOLFIRI	Irinotecan 5-FU Folinic acid	2	yes	yes
	Monotherapy	Irinotecan	3	no	no

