#### UGT1A1 genotyping in blood samples and adaptation of irinotecan dose intensity

Before treatment initiation, the *UGT1A1* genotype of the patient will be assessed in blood using Polymerase Chain Reaction (PCR). Patients will be genotyped for *UGT1A1*28* (TA repeat; rs3064744; NC_000002.12:g.233760235TA[5_11]). DNA for genotyping will be isolated from 200µl of whole EDTA blood obtained prior to start of therapy. Genotyping will be conducted using validated real-time PCR reactions with appropriate wild type, heterozygous and homozygous controls in every run. Genotypes will be converted to phenotypes in the following manner: homozygous carriers of *UGT1A1*28* are defined as UGT1A1 PMs, heterozygous carriers are considered UGT1A1 intermediate metabolizers (IMs) and *UGT1A1* wild type individuals are considered UGT1A1 normal metabolizers (NMs). In UGT1A1 PMs the irinotecan starting dose will be reduced by 30% and further individualized in subsequent cycles of treatment based on ANC and clinical tolerance. The starting dose in UGT1A1 NMs and IMs will be left unchanged. Further dose modifications or treatment delays will be applied according to standard of care protocols and guidelines.

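### The concurrent comparison behind the UGT1A1 poor-metabolizer safety objective takes comparable toxicity as its premise, and the trial is too small in this subgroup for non-difference to show similarity

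*Protocol article*

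**What the plan says.** Aims of the study lists as a primary objective: "To validate the safety of *UGT1A1* genotype-guided dose adaptation (70% dose intensity) in UGT1A1 PMs".

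Statistical and bioinformatic analysis of main outcome parameters gives two comparisons for it:

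- The first is external: "toxicity in UGT1A1 PMs will be compared to historical control patients", meaning published cohorts of *UGT1A1\*28* homozygotes who received full-dose therapy.
- The second is concurrent: "toxicity in UGT1A1 PMs will be compared to UGT1A1 non-PMs treated with full dose in the current study", and this is done "under the assumption that these groups experience comparable degrees of toxicity".

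The Discussion says how a favourable result would be read. "If a 70% dose intensity in UGT1A1 PMs leads to similar incidences of severe toxicity as compared to UGT1A1 NMs and IMs" on full dose, that is taken as further support for the biomarker.

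Sample size calculation rests only on the precision of sensitivity and specificity of the GUS activity assay: 84 evaluable patients, 104 enrolled. It does not mention PMs.

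**The concern.** Comparable toxicity in PMs on the reduced starting dose and in full-dose non-PMs is what the concurrent comparison would have to demonstrate. Taken as a premise, it leaves the comparison nothing to test. Taken as a loosely worded hypothesis, it becomes a similarity claim. Such a claim needs an interval narrow enough to exclude an unacceptable excess; the absence of a detected difference is not enough.

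The risk is false reassurance on a primary safety objective. Similar observed rates in a small subgroup could be presented as support for a dosing strategy while the same data remained compatible with a large excess of severe toxicity in PMs. The Discussion expects the study's results to inform clinicians' choices, including dose adjustments.

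**Working it through.** **Inputs from the protocol article.** Grade 3–4 neutropenia 46% and grade 3–4 diarrhea about 18% (Background); 84 evaluable and 104 enrolled patients (Sample size calculation).

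**Input that is assumed.** The share of PMs is not stated. I take 5–15%, which gives 4–13 PMs among 84 or 5–16 among 104.

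**The plan's own precision figures.** These concern the GUS assay. With 22 cases and an assumed sensitivity of 80%, 1.96 × √(0.80 × 0.20 / 22) = 16.7 points, against a stated 17. With 62 non-cases and an assumed specificity of 80%, 1.96 × √(0.80 × 0.20 / 62) = 10.0 points, against about 10. Dropout: 84 / 0.80 = 105, against 104. No corresponding figure exists for the PM comparison.

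**Precision of the PM versus non-PM difference.** With equal true rates p, the half-width is 1.96 × √[p(1 − p)(1/n₁ + 1/n₂)]. For neutropenia (p = 0.46), using expected counts:

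- 5% of 84: 4.2 vs 79.8 gives 48.9 points
- 10% of 84: 8.4 vs 75.6 gives 35.5 points
- 10% of 104: 10.4 vs 93.6 gives 31.9 points
- 15% of 104: 15.6 vs 88.4 gives 26.8 points

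The table uses whole patients, so its extremes differ slightly. The last column is two-sided Fisher exact power at the 5% level.

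| PM vs non-PM | Half-width, p = 46% | Half-width, p = 18% | Power, 36% vs 18% |
|---|---|---|---|
| 4 vs 80 | 50.0 | 38.6 | 12.4% |
| 8 vs 76 | 36.3 | 28.0 | 21.6% |
| 13 vs 71 | 29.5 | 22.7 | 25.6% |
| 5 vs 99 | 44.8 | 34.5 | 15.1% |
| 10 vs 94 | 32.5 | 25.0 | 25.8% |
| 16 vs 88 | 26.5 | 20.5 | 30.8% |

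With 4 or 5 PMs the normal approximation is rough, so the widest half-widths indicate order of magnitude only.

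**Other excesses at 10 vs 94.** Neutropenia of 70% vs 46% is detected with 27.9% power, and 92% vs 46% with 88.4%.

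**PMs alone.** With 0 severe events in 10 PMs, the exact 95% upper limit is 1 − 0.025^(1/10) = 30.8%.

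**Best case, free of the prevalence assumption.** Split all 104 patients 52:52. The half-width is 1.96 × √(2 × 0.46 × 0.54 / 52) = 19.2 points for neutropenia and 1.96 × √(2 × 0.18 × 0.82 / 52) = 14.8 points for diarrhea.

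**What a similarity claim would need.** Take a 15-point margin, purely as an illustration, with equal true rates, one-sided 2.5% and 80% power. The number per group at 1:1 is (1.96 + 0.84)² × 2p(1 − p) / 0.15², which is 103 at 18% and 174 at 46%. Power to exclude a 15-point excess is 12–30% (diarrhea) and 9–20% (neutropenia) over the assumed PM shares. With 52:52 it is 51% and 34%.

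**The case against.** **The historical comparison comes first and does not assume equality.** This is correct. A reader might infer that the whole safety objective is circular, but only the concurrent comparison carries the premise. The historical comparison does not rescue the word validate, however, because it uses the same few PMs and sets them against non-concurrent literature cohorts.

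**Assumption may simply mean expectation.** That is a fair reading, and it removes the circularity. It does not remove the need to show similarity with an adequate interval.

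**No sentence says that similar toxicity means safety is validated.** This is also true. Validation is the stated aim; the Discussion claims only further support for the biomarker. That absence of a difference would be reported as validated safety is an inference about future reporting.

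**A null result is not a foregone conclusion.** A reader might infer from the small numbers that one is almost guaranteed. The figures do not bear this out: with 10 PMs, neutropenia of 92% vs 46% would be found with 88% power. Low power applies to moderate excesses, including a doubling of severe diarrhea.

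**The number of PMs is unknown.** The small subgroup rests on an assumed prevalence, but the 52:52 case shows that the conclusion does not depend on it.

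**A margin may stand in a full protocol or SAP.** It may, and its absence from the article is not counted here. A margin would not alter the stated premise, the confirmatory wording or the number of patients.

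**The comparator's dose.** Study population admits patients whose starting dose is reduced by up to 25%, while the genotyping section says "The starting dose in UGT1A1 NMs and IMs will be left unchanged". A reader might infer a contradiction. The passages can be read together: the genotyping section concerns changes made for genotype, and the analysis section names full-dose non-PMs as the comparator within a wider cohort. At most a clarification is due.

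**Conclusion.** The point stands for the concurrent comparison and for the confirmatory wording of the objective. As written, comparability is a premise, and similar observed rates would count as support in a subgroup for which the trial was not sized. With 5–15% PMs (an assumption), the uncertainty is about ±27 to ±49 points for neutropenia at 46% in both groups, and power against a doubling of severe diarrhea is about 12–31%. With the most favourable split possible, ±19 and ±15 points remain. The study can estimate PM toxicity imprecisely and may reveal a very large excess; it is poorly placed to establish similarity. No view is taken on the dose itself.

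**What to change.** - Restate the objective as estimating toxicity in PMs on the reduced starting dose, and align the analysis section and Discussion with it.
- Delete the premise of comparable toxicity.
- Report grade 3 or higher neutropenia and diarrhea in PMs with exact 95% confidence intervals, and the risk difference versus non-PMs with its interval.
- Claim similarity only if the upper limit of that difference lies below a margin fixed beforehand; otherwise call the result inconclusive.
- Present the literature comparison as descriptive.
- For clarity, state that the concurrent comparator is the full-dose subset of the non-PMs whom the eligibility criteria admit.

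The cost is rewording. No patients, samples or assessments are added, but the conclusion will be weaker than validation.
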